## Abstract

**Background:**

Hypertension (HTN) is a major public health concern in the United States given its wide prevalence, high cost, and poor rates of control. Multiple strategies to counter this growing epidemic have been studied, and home blood pressure (BP) monitoring, mobile health (mHealth) interventions, and referrals to clinical pharmacists for BP management have all shown potential to be effective intervention strategies.

**Objective:**

The purpose of this study is to establish feasibility and acceptability of BPTrack, a clinical pharmacist-led mHealth intervention that aims to improve BP control by supporting home BP monitoring and medication adherence among patients with uncontrolled HTN. BPTrack is an intervention that makes home-monitored BP data available to clinical pharmacists for use in HTN management. Secondarily, this study seeks to understand barriers to adoption of this intervention, as well as points of improvement among key stakeholders, so that larger scale dissemination of the intervention may be achieved and more rigorous research can be conducted.

**Methods:**

This study is recruiting up to 25 individuals who have poorly controlled HTN from a Family Medicine clinic affiliated with a large Midwestern academic medical center. Patient participants complete a baseline visit, including installation and instructions on how to use BPTrack. Patient participants are then asked to follow the BP monitoring protocol for a period of 12 weeks, and subsequently complete a follow-up visit at the conclusion of the study period.

**Results:**

The recruitment period for the pilot study began in November 2016, and data collection is expected to conclude in late-2017.

**Conclusions:**

This pilot study seeks to document the feasibility and acceptability of a clinical pharmacist-led mHealth approach to managing HTN within a primary care setting. Through our 12-week pilot study, we expect to lend support for this approach, and lay the foundation for translating this approach into wider-scale implementation. This mHealth intervention seeks to leverage the multidisciplinary care team already in place within primary care, and to improve health outcomes for patients with uncontrolled HTN.

**Trial Registration:**

Clinicaltrials.gov NCT02898584; https://clinicaltrials.gov/ct2/show/NCT02898584 (Archived by WebCite® at http://www.webcitation.org/6u3wTGbe6)

## Introduction

### Background and Significance

Hypertension (HTN) is a serious public health concern in the United States, affecting approximately 78 million adults and burdening the health care system with an estimated US $42.9 billion in direct costs in 2010 [1,2]. HTN is a key risk factor for heart disease and stroke, which are the first and fourth leading causes of death in the United States, respectively [3]. Of patients with HTN, it is estimated that only approximately 50% achieve blood pressure (BP) control, and approximately 20% remain unaware of their condition [1]. Given the prevalence and high cost of HTN, coupled with poor rates of control, identifying strategies to assist patients in managing their HTN is imperative.

An important and effective strategy for HTN management is home BP monitoring [4-7], yet problems with data quality and latency can be abundant when patients maintain paper-based logs for self-monitoring [8,9], potentially compromising the effective and efficient use of paper-based logs in primary care. Additionally, clinical pharmacists can help manage chronic conditions such as HTN in primary care settings [10,11] and have themselves been shown to be an effective intervention for patient HTN management [12,13]. Despite evidence suggesting the efficacy of home BP monitoring and clinical pharmacists for HTN management, neither strategy is being widely used in primary care settings.

One potential solution that shows great promise is the use of mobile health (mHealth) approaches to bridge the gap between home monitoring and clinical pharmacist care. Approximately 95% of American adults have a cell phone, 77% have a smartphone, and the rate of smarphone adoption is increasing rapidly [14]. Moreover, the majority of individuals living with one or two chronic conditions report tracking at least one health indicator (70% and 80% respectively); a task that is greatly supported through the use of mobile technology [15].

mHealth interventions may therefore be a viable strategy to close the loop between patient self-monitoring and clinician management, thus potentially improving HTN management. The current utility of such interventions is often reduced however, as they are typically patient-facing and do not support bidirectional patient-provider communication. However, through a bidirectional intervention in which patient-provider interaction and automatic transmission of electronic data from home BP monitors to clinicians can occur in real-time, mHealth interventions may be a practical solution. Efficiencies in patient management could potentially lead to increases in the number of hypertensive patients that a clinical pharmacist could manage, as well as improvements in the quality of patient BP management. Moreover, mHealth interventions often contain other features that have been linked to chronic disease self-management, including data tracking, general/tailored education, and reminders, all of which may contribute to improved HTN control [16,17].

### Study Objective

The purpose of this study is to establish feasibility and acceptability of BPTrack, which is a clinical pharmacist-led mHealth intervention that supports home BP monitoring and medication adherence among patients with uncontrolled HTN, and makes collected data available to the pharmacist for use in HTN management. Secondarily, this study seeks to understand barriers to adoption, as well as points of improvement among key stakeholders, so that larger scale dissemination of the intervention may be achieved, and more rigorous research can be conducted.

## Methods

### Overview

We are currently conducting a 12-week pre/postintervention pilot study of BPTrack, a clinical pharmacist-led mHealth intervention, which seeks to improve BP control among uncontrolled hypertensive patients recruited from a primary care setting, and who are receiving treatment for their HTN under the care of a clinical pharmacist embedded in the primary care clinic. The final protocol closely mirrored what was originally proposed to the funder (see Multimedia Appendix 1 and Multimedia Appendix 2 for original review scoring forms). The methods for this study have been approved by the University of Michigan IRBMED Institutional Review Board (HUM00105772).

### BPTrack Intervention Description

The BPTrack intervention supports patient home BP monitoring and medication adherence tracking for sharing with a clinical pharmacist. BPTrack consists of two different mobile apps developed by the Tactio Health Group and modified from their TactioRPM Platform; one for the patient, and one for the clinical pharmacist. These modified mobile apps are intended for our research purposes only, have been rebranded with appropriate program logos, and are distributed by the University of Michigan via the Apple and Google Play app stores.

BPTrack is a patient-facing smartphone app for iOS and Android that supports home BP monitoring, medication adherence, and communication with a clinical pharmacist who is managing patients’ HTN. BPTrack allows people to measure their BP using a compatible Bluetooth-enabled BP cuff (this study provides patient participants with a Welch Allyn Remote Monitoring Upper Arm Blood Pressure Device RPM-BP100), after which the BP reading is automatically synced with the BPTrack smartphone app, and transmitted to a secured cloud server. Individuals can also manually enter their BP data into the app, without syncing the BP cuff. Within the visual display, patient participants are provided a graph of their BP data over time (Figure 1), as well as mean, minimum, and maximum values for systolic BP (SBP), diastolic BP (DBP), and pulse. Color-coded data points on the graph highlight how a BP value compares to BP target goals; two hues of green represent normal BP or prehypertension, orange represents stage 1 HTN, and red represents stage 2 HTN (refer to Table 1 for actual assigned SBP and DBP ranges within BPTrack). To self-monitor medication adherence, BPTrack sends daily medication reminders that are coupled with educational messages focused on the importance of medication adherence for managing HTN (Figure 2). In addition, users can record their adherence data in free text via a *Notes* feature. Finally, BPTrack provides a mechanism to send in-app messages directly to the clinical pharmacist.

BPTrack Pharm is a mobile app for the iPad, which is used by clinicians to monitor collected BP and medication adherence data from patients using the BPTrack app. BPTrack Pharm presents clinicians with a color-coded dashboard view to quickly highlight all enrolled patients’ BP control (Figure 3), as well as a more detailed view for each individual patient, which allows the clinical pharmacist to view all collected BP and adherence data for each enrolled patient (Figure 4). BPTrack affords clinicians the ability to set custom BP goals for individuals, and to directly message a patient via the app.

**Table 1 table1:** Assigned SBP and DBP ranges for blood pressure categorization in BPTrack.

Category	Color	Systolic Blood Pressure	Diastolic Blood Pressure
Optimal	Green	<120 mmHg	<80 mmHg
Prehypertension	Light green	≥120 mmHg to <140 mmHg	≥80 mmHg to <90 mmHg
Stage 1 Hypertension	Orange	≥140 mmHg to <160 mmHg	≥90 mmHg to <100 mmHg
Stage 2 Hypertension	Red	≥160 mmHg	≥100 mmHg

**Figure 1 figure1:**
[figure not shown]
BPTrack blood pressure graph screen.

### BPTrack Theoretical Underpinnings

Our approach to HTN management, which relies on daily BP and medication adherence self-monitoring, is rooted in a self-regulatory framework. In the theory of self-regulation, individuals participate in self-directed behaviors, thought to be managed through a dynamic feedback loop. In this loop, individuals process information about their past behavior and integrate the information into goals and motivation to change future behaviors (ie, self- monitoring) [18]. By engaging in daily BP and medication adherence self-monitoring, patient participants will have the opportunity to see progress made toward meeting BP goals, which (when combined with self-reflection on behaviors) should tap into the dynamic feedback loop to lead to possible behavior change.

**Figure 2 figure2:**
[figure not shown]
BPTrack medication reminder screen.

### Setting

This pilot study is being conducted with patients at a Family Medicine clinic affiliated with a large Midwestern academic medical center. The participating site generates over 29,000 patient visits annually (72% of which are adult visits) and serves a predominantly blue-collar, underserved African-American and Hispanic population. HTN is a prevalent chronic condition that is treated at the recruiting clinic.

### Sample

We are enrolling up to 25 patient participants for this pilot study. To be eligible for participation, enrollees must be ≥18 years of age, have a smartphone compatible with the mobile intervention, have been previously diagnosed with HTN, have uncontrolled HTN (SBP >140 mmHg and/or DBP >90 mmHg on repeat measurements), be under the care of a primary care physician at the recruiting clinic, be taking at least one antihypertensive medication, and be English-speaking.

**Figure 3 figure3:**
[figure not shown]
BPTrack Pharm main screen.

Potential enrollees are excluded if they are >65 years of age, are already under the care of a clinical pharmacist for HTN management or under the care of a cardiologist, are pregnant, have serious existing medical conditions that may make BP control difficult or necessitate frequent hospitalization (such as previous diagnosis of resistant HTN, steroid dependent asthma or emphysema, cirrhosis or hepatic failure, stage C or D chronic heart failure, stage IV or V chronic kidney disease, and terminal cancer or ongoing active chemotherapeutic or radiation therapy), or have other serious medical conditions (eg, stroke, dementia) that may affect their ability to self-monitor their BP.

### Recruitment

Patient participants are recruited through recruitment flyer dissemination by clinic staff (physicians, medical assistants, clinical pharmacist, or other clinic staff) to potentially eligible participants, as well as targeted recruitment letters. To facilitate provider and staff referral, study flyers were provided to clinic staff and providers so that they can be handed directly to potentially eligible individuals as they are seen in clinic. Moreover, study staff are providing primary care physicians with lists of potentially eligible patients, identified through the electronic medical records system, who are scheduled to be seen in the clinic. The clinical pharmacist on this study is also directly recruiting patients who meet eligibility criteria. Recruitment flyers list a study hotline that individuals must call in order to be screened for participation in the study.

In order to send targeted recruitment letters, study staff are conducting automated pulls of patient data from electronic health records to obtain mailing lists of patients at the recruiting site who meet clinical eligibility criteria. These targeted recruitment letters inform recipients that they are potentially eligible for a research study focused on HTN management and that they may receive a phone call to solicit their participation. In addition, recruitment letters provide contact information for study staff so that interested individuals can directly contact the team. Shortly after recruitment letters are distributed, study staff are calling potentially eligible participants to solicit participation.

### Procedures

Any individual patient at the recruiting site who expresses interest by calling the study hotline is subsequently screened by phone. Once screened as eligible, patient participants are scheduled for an informed consent and baseline data collection appointment with study staff at the recruitment site, or another affiliated space. These visits take approximately 90 minutes to complete.

**Figure 4 figure4:**
[figure not shown]
BPTrack Pharm individual screen.

After baseline data collection is complete, study staff help patient participants download the intervention app onto their smartphone, and train them on how to use the app. Participants are also given a Bluetooth-enabled BP monitor to take home, and are instructed on how to use it, as well as how to sync it to BPTrack. All BP monitors are checked before the patient participant leaves the baseline data collection visit, and are tested against a manual BP reading taken by a trained study staff member. Although we are not calibrating the home BP monitors, we do look to see how well their readings compare with the manual BP readings. Once enrolled in the study, the clinical pharmacist sees patient participants as needed for ongoing HTN management.

Patient participants are also instructed on the BP monitoring protocol that we will adhere to in this study, and are instructed to take three consecutive BP readings twice daily, at varying times across days. Prior to BP monitoring, patient participants are instructed to: go to the bathroom before taking their BP, if needed; keep their arm at heart level by resting it on a table during monitoring; sit in a chair with a back, with feet flat on the floor for at least five minutes prior to monitoring; avoid tobacco, caffeine, or alcohol for 30 minutes prior to BP monitoring; avoid taking their BP immediately after exercise, when emotionally upset, or in pain; and to avoid talking while taking their BP.

In the event that a patient participant has an SBP >160 mmHg, SBP <100 mmHg, DBP >100 mmHg, or DBP <60 mmHg, they are instructed to wait five minutes and then recheck their BP using the previously described protocol. Patient participants are also instructed that if BP readings exceed these critical thresholds for three days in a row, they should contact the clinic. Finally, patient participants are instructed to call the clinic immediately if they are experiencing symptoms of dizziness, chest pain, severe headache, or visual changes.

Patient participants are instructed to follow the home BP monitoring protocol for 12 weeks, to ensure that the BP readings sync with the BPTrack app, and to self-monitor BP medication adherence. During this 12-week intervention period, the project’s clinical pharmacist monitors home BP and medication adherence readings through the BPTrack Pharm clinician app, and manages patient participant HTN in concordance with their normal clinical practice. In the event that a patient participant exhibits continued elevated BP readings, the clinical pharmacist contacts them to determine whether the patient needs to come in to the clinic for follow-up, or whether to continue to monitor through the app. The clinical pharmacist is exercising their best clinical judgment in managing the research participants’ BP.

At the conclusion of the 12-week intervention period, patient participants meet with study staff for their 12-week follow-up data collection visit, which takes approximately 60 minutes to complete. At this visit, the patient participants complete the Adherence to Refills and Medications Scale (ARMS) [19], they are asked to bring in all antihypertensive medications for a pill count, and interviews are audio recorded.

To compensate patient participants for their participation in the study and to reduce attrition, individuals receive US $25 upon completion of their 12-week follow-up data collection visit. Patient participants are also allowed to keep the BP monitor used in the study (valued at approximately US $100/monitor). In addition to incentives offered for participation, additional retention strategies implemented in past and current projects are being used, such as routinely obtaining contact information for the participant and up to three friends/relatives who can help locate them, as well as baseline and follow-up appointment reminders via phone and/or email. Individuals who leave the study early are compensated on a pro-rated basis, and are required to return the BP monitor.

After the study has finished, we will conduct interviews with the study’s clinical pharmacist and other key stakeholders at the recruiting clinical site. Key stakeholders will be recruited through direct solicitation via email and phone calls; these stakeholders are expected to include clinic medical directors, primary care physicians, health systems administrators, and information technology personnel. These interviews will be audio recorded and transcribed for further analysis.

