### Statistical Analysis Plan

Descriptive statistics will be used to describe patient participant characteristics and perceptions, mHealth utilization, and clinical pharmacist utilization and perceptions. Categorical data will be displayed as frequencies and percentages, and Chi-square tests will be used for comparisons. SBP and DBP will be expressed as mean (standard deviation) and pre/postintervention BP means will be compared using 2-tailed paired samples t-tests.

The effect of clinical pharmacist contact with patient participants will be evaluated through changes in utilization of the mHealth app and changes in BP levels surrounding the time of contact. Models will be used to separately evaluate SBP and DBP levels over time, including pharmacist contact as a time-varying covariate using a mixed-effects regression approach. The mixed-model analysis accounts for the correlation of BP measures on the same individual across time. Similar analyses will be carried out on daily utilization of the mHealth app. Daily usage will be coded as a binary response and modeled using generalized estimating equations, including pharmacist contact with patient participants as a covariate to identify the odds of app usage before and after contact.

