### Limitations

Perhaps the largest limitation of this pilot study is our limited sample size, which was chosen due to the pragmatics of recruitment and budgetary constraints. As highlighted by Leon et al, “the primary role of a pilot study is to example the feasibility of a research endeavor” [21]. Our intended sample size is large enough to satisfy the rule of thumb of 12 participants per group (set forth by Julious et al [22]) as appropriate for guiding sample size selection for pilot studies. Although we may not have adequate power to detect effects, this is a true feasibility trial in which we will be able to obtain preliminary data to support and plan for future implementations. Feasibility will be assessed on many different levels, including the feasibility of using BPTrack amongst our target population, within the primary care setting, and within the health system. In addition, the lack of a control or other comparison group is a limitation of our study design; however, given that this is a pilot study to preliminarily investigate the use of this approach in a clinical setting, our single group design is warranted. Future work should seek to incorporate a more robust research design.

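### Home BP is measured at deliberately varied hours, but the mixed model for SBP and DBP names no time-of-day term: some added noise, and a possible false shift of about 0.5 to 2 mmHg if the morning/evening balance changes

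*Protocol article*

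**What the plan says.** The Procedures section sets the home schedule: patients are "instructed to take three consecutive BP readings twice daily, at varying times across days". It also states that "Patient participants are instructed to follow the home BP monitoring protocol for 12 weeks". The same section standardises bladder, arm position, seating, rest, tobacco, caffeine, alcohol, exercise and talking. Clock time is the one condition it deliberately varies, and it gives no reason.

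The Statistical Analysis Plan section says: "Models will be used to separately evaluate SBP and DBP levels over time, including pharmacist contact as a time-varying covariate using a mixed-effects regression approach". It adds that the mixed model handles the correlation of measures within a person. Pharmacist contact is to be judged through "changes in utilization of the mHealth app and changes in BP levels surrounding the time of contact".

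The Blood Pressure section provides manual clinic readings at baseline and week 12 only, so a model of BP around contacts has to use the home readings. The intervention description says that after a measurement "the BP reading is automatically synced with the BPTrack smartphone app, and transmitted to a secured cloud server", and it also allows manual entry without syncing.

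**The concern.** BP varies with the time of day. Every participant takes at least one antihypertensive drug (Sample section), so it may also vary with time since the last dose. With no clock-time term, a morning and a late-evening reading count as measures of the same level. Two consequences follow.

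- **Noise.** Clock-time variation goes into the residual.
- **Confounding.** If the hours of measurement change systematically with study week, or from before to after a contact, that change is read as a change in BP. A random effect for the patient, or a within-person correlation structure, does not remove it.

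The contact analysis is the more exposed of the two. The same section plans to test whether contact changes daily app use, so the plan itself allows that measuring behaviour may change at contact. If contact brings back sessions of one kind (say, skipped mornings), the time-of-day mix changes exactly where the BP effect is estimated.

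**Working it through.** The plan states no figure to reproduce here. Its only sizing statement compares up to 25 patients with a rule of thumb of 12 per group, and the point does not depend on it.

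**Inputs from the protocol.** Two sessions a day for 12 weeks: 2 × 84 = 168 sessions per patient; up to 25 patients; one group.

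**Assumptions (not in the documents).** The clock-time component is A·cos(2π(h − p)/24), where h is clock hour, p the peak hour and A half the peak-to-trough swing. The other session-level SD is 8 mmHg. Two settings were used:

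- Setting 1: p = 15:00, A = 4 to 8, mornings uniform over 05–11 h, evenings uniform over 16–23 h.
- Setting 2: p = 16:00, A = 3 to 8. Times are uniform over 07–22 h for the noise figure; sessions are at 08:00 and 20:00 for the shift figures.

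**Noise.** Session SD = √(8² + SD_clock²).

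| Setting | A | SD_clock | Session SD | Rise |
|---|---|---|---|---|
| 1 | 4 | 2.07 | 8.26 | 3% |
| 1 | 8 | 4.13 | 9.00 | 13% |
| 2 | 3 | 1.49 | 8.14 | 2% |
| 2 | 5 | 2.48 | 8.38 | 5% |
| 2 | 8 | 3.97 | 8.93 | 12% |

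In setting 2 the SE of a 7-day mean (14 sessions) goes from 8/√14 = 2.14 to 2.17, 2.24 and 2.39.

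**One session moves 2 h later, the other stays.**

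- Setting 1: the evening mean goes from 0.331A to −0.113A, a change of −0.444A. The daily mean covers both sessions, so it moves by half of that, −0.222A: −0.9 mmHg at A = 4 and −1.8 at A = 8. The evening mean alone moves by −1.8 to −3.6.
- Setting 2: the evening value goes from A·cos 60° = 0.5A to A·cos 90° = 0. Half the change is 0.25A: 0.75, 1.25 and 2.0 mmHg for A = 3, 5 and 8. A morning-only shift gives the same size with the opposite sign.

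**Morning share falls from 50% to 30%** (setting 1). The change is 0.20 × (0.331A − (−0.233A)) = 0.113A: 0.45 mmHg at A = 4 and 0.90 at A = 8. At A = 3 it would be 0.34.

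**Both sessions move 2 h later.**

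- Setting 1: mornings change by +0.466A and evenings by −0.444A. Half the sum is 0.011A: 0.04 to 0.09 mmHg.
- Setting 2: the changes are +0.5A and −0.5A, which cancel.

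**Simulation.** 25 patients × 84 days × 2 sessions, no true mean trend, p = 16:00, mornings 06–11 h, evenings 16–22 h, 120 runs per scenario. The mean of per-patient slopes stood in for the mixed model.

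- Times random and unrelated to study day: false 12-week change within ±0.13 mmHg, which is about simulation error.
- Both sessions drifting 2 h together: mostly 0.0 to 0.3 mmHg in size. The largest was 0.58, for A = 8 with both sessions drifting earlier. Cancellation is incomplete there because the window centres (08:30 and 19:00) are 10.5 h apart, not 12.
- With cosine and sine terms for clock time: within about ±0.1 mmHg in every scenario.

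The SE of the mean 12-week change was about 0.8 to 1.0 mmHg. Most of that comes from an assumed between-patient slope SD of 0.05 mmHg per day (0.05 × 83/√25 = 0.83), so the extra session noise matters little for a trend. A false shift of 1 to 2 mmHg is as large as, or larger than, that SE.

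**The case against.** The strongest reply is that this is only a missing covariate. A journal article may leave the full covariate list to an analysis plan that is not shown, and the sentence on the mixed model does not close the list. That stands: silence alone would be no finding, and if the plan already includes time of day, one sentence settles the point. What remains is that the article itself fixes a rule that varies measuring time, and the terms it names do not deal with the result.

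A reader might infer that any drift in measuring hours appears as a BP trend. The arithmetic does not support that: random variation gives none, and a common shift of both sessions nearly cancels. A reader might also take 1.8 to 3.6 mmHg as the bias. That is the evening mean alone; the daily mean moves by half as much.

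It is also true that one-sided shifts and lost sessions can occur under a fixed-time instruction, so the rule does not by itself create the bias. The section names no 12-week trend estimate as a result. No document figure shows that hours do shift around contacts. Finally, the stated purpose is feasibility and acceptability, and the Limitations section concedes that power may be inadequate. These limit the weight of the point. They do not remove it for the contact analysis, which the plan names and whose behavioural side it proposes to test.

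**Conclusion.** The point holds in a limited form. Under assumed amplitudes of 3 to 8 mmHg and a session SD of 8 mmHg, leaving out clock time raises session SD by roughly 2% to 13%. It gives little or no false trend when times vary at random or both sessions move together. A one-sided 2-hour shift, or a morning share falling from 50% to 30%, can move the daily mean by about 0.5 to 2 mmHg with no true BP change. The upper end needs the largest amplitude and the same one-sided shift in every patient.

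The pre/post paired t-test is not affected on the natural reading, in which it compares the two manual clinic measurements. Nothing in the documents shows that the sampling rule is wrong; varying the hours may be meant to cover the whole day. All magnitudes rest on the assumed cosine rhythm, because the documents give no figure for daily BP variation.

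**What to change.** Keep the sampling rule and change the analysis:

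1. Average the readings of each session before modelling.
2. Add time of day to the SBP and DBP mixed models, either as a morning/evening factor plus clock hour or as a 24-hour sine/cosine pair. The contact effect, and any time trend reported, are then adjusted for it.
3. Report the distribution of measuring times by study week and before and after contact, so that a reader can see whether the mix moved.

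The cost is one or two extra terms per model and one descriptive table, with no change for patients. The fix assumes that readings carry time stamps. Automatic syncing, the in-app graph and the planned log-file analysis imply this, but the article does not say so. Manually entered readings may lack a reliable time, so a sensitivity analysis without them is needed. Time since dose stays unaddressed unless dose times are recorded; where they are, it could be added in the same way.
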